**Exclusion criteria**

- Women who are not recruited to the MOLI RCT
- Women who lack the capacity to make an informed decision
- Women under the age of 16
- Women who have had a stillbirth in this pregnancy
- Women who are distressed/in pain
- Women too unwell to take part in interviews, or who need urgent intervention (in less than 2 hours)
- Where delay in starting the IOL process due to time of interview could cause harm to the patient
- Women who do not give consent to be in the study

## MOLI practitioners

**Inclusion criteria**

- Practitioners who are involved in screening, recruiting, randomising and consenting participants to MOLI RCT

**Exclusion criteria**

- Staff who do not wish to be included
- Staff who do not give their consent to participate

# Recruitment

**Patients** - Initial contact with potential qMOLI participants will be made by the RCT recruitment team. After recruitment to the MOLI RCT, women will be asked whether they would like to speak to a qualitative researcher about this additional aspect of the research.

If the MOLI recruit is willing to speak to the qMOLI researcher, then a research assistant will attend and discuss the qMOLI study. As well as verbal information, patients will also receive a patient information sheet in Hindi, Marathi or English and asked if they would like to participate. The PIS will be translated and back translated into Hindi and Marathi, in order to check accuracy. As with the main MOLI study, there is limited time for patients to consider entering the qMOLI study. This will vary according to the clinical scenario and urgency of IOL, but one hour is likely to be the maximum. Women who are unsure will therefore not be recruited to the study. If the patient is agreeable, recruitment and written consent will take place, in the patients’ own language. Separate written consent for qMOLI is necessary (see appendix), as it is a separate study to the MOLI RCT. Many more women will take part in the RCT than the qualitative study. Further opportunities to ask questions will be offered throughout this process.

**Staff -** The focus group discussions will be advertised, and information leaflets will be distributed so staff will have time to consider if they wish to participate. At the initial MOLI RCT training, the focus group element part of the study will be explained to staff. Those who register interest will be given a practitioner information sheet including details of topics that will be discussed in the focus group, duration of the group and location for the group. If a staff member decides to participate they will be asked to sign a consent form. They will also receive a letter after the focus group thanking them for their participation.

- colleagues experienced in qualitative interviews in pregnant and postpartum women and
- colleagues who have experience of working with pregnant women in India.

**Staff** – Focus group discussion will be conducted in English, using interview guides to ensure that all topics are covered but allow flexibility to explore participants views. The interview guides are attached in the appendix of this protocol.

# Analysis

The framework analysis approach uses stages for analysis [26].

**Stage 1 – Transcription**

A verbatim (word for word) transcription of the interview will be taken from the audio recording. The transcripts will be uploaded onto NVIVO 12 software and then checked by researchers who conducted the interview. Transcripts will have large margins and adequate line spacing for appropriate coding and marking notes.

**Stage 2 – Familiarisation with the interview**

Both researchers will review the transcript and audio recording and ensure any contextual/reflective notes are included.

**Stage 3 – Coding**

This is an inductive evaluation, so open coding will be used to label anything which might be relevant. Codes could represent things, values, emotions and more impressionistic/methodological elements. This coding classifies the data, so it can be compared with the whole data set systematically. Each line will be reviewed individually looking for codes. At least the first few transcripts from each group will be independently coded by both researchers. Any differences will be discussed, and a consensus reached.

**Stage 4 – Developing a working analytical framework**

After coding the first few transcripts and each group of transcripts the researchers will meet to compare labels and agree on a set of codes to apply to the other transcripts. Codes will be grouped into categories, which are then clearly defined. Several iterations of this will be performed until no further codes emerge. An “other” code will be used to avoid missing any data.

**Stage 5 – Applying the analytical framework**

This working framework is then applied by indexing existing categories and codes. Each code will be assigned a number using the N-VIVO software.

**Stage 6 – Charting data into the framework matrix**

A spread sheet will be used to chart the data into a matrix via N-VIVO. The chart will include links to interesting or illustrative quotes.

**Stage 7 – Interpreting the data**

Characteristics and differences in the data will be identified, the researchers will then aim to map these and explore relationships and causality.

The data from each group of participants will be analysed separately and then merged.

Rigor and transparency will be maintained throughout the whole process by the research team conducting regular meetings to discuss the data.

# Consent

If the patient is agreeable to considering entry into the qualitative study (after recruiting and consenting to join the MOLI RCT), the research assistant will give them a patient information sheet in her own language to read. She will be given the opportunity to discuss her possible participation with her relatives, or friends or their legal representative or with staff experienced in obtaining informed consent. Then the q MOLI team will approach them on the ward.

The qualitative team will fully explain the study and answer any questions, whilst adhering to the principles of GCP, which have their origin in the Declaration of Helsinki.

Discussion will include:

- conversation between the potential participant or her legally acceptable representative and an individual knowledgeable about the research, about the nature and objectives of the study and possible risks associated with their participation, time commitments and data handling/access
- the presentation of written material (information sheet and consent documents)
- the opportunity for potential participants to ask questions
- assessment of capacity. A capable person will:
  - understand the purpose and nature of the research
  - understand what the research involves, its benefits (or lack of benefits), risks and burdens and ask appropriate questions
  - understand the alternatives to taking part
  - be able to retain the information long enough to make an effective decision.
  - be able to make a free choice
  - be capable of making this particular decision at the time it needs to be made
  - it is important that the patients understand that their interests will be protected and that they are not being coerced.

If the woman decides to participate then she will be asked to sign a consent form. In the event that a woman is not literate, the patient consent form (PCF) and information sheet will be read to her by the researcher. Upon reviewing the document, the researcher will explain the research study to the patient. This information will emphasise that participation in the trial is voluntary and that the participant may withdraw from the trial at any time and for any reason, without patient care being affected. All participants will be given an opportunity to ask any questions that may arise, have the opportunity to discuss the study with their friends/family member/doctor and time to consider the information prior to agreeing to participate. A contact point where further information about the trial may be obtained will be provided. Some Indian women may not be able to sign their own name but would be willing to place a finger/thumb print on the PCF. The PCF will be printed in triplicate; the original copy will be filed in the site office in the site file, a copy of the PCF will be given to the patient for their records and another copy in the patient’s notes.  Separate consent forms will be used for the MOLI RCT and qualitative study. The q MOLI documentation will be kept in a separate file, in a separate locked cabinet, in the MOLI site offices, than the main MOLI documentation.

# Ethical and Regulatory Considerations

A full suite of data management plans and SOPs have been written, audited and approved for the MOLI RCT by the trial sponsor, the University of Liverpool and these will be used, where relevant for the qualitative study.

The study will be conducted in accordance with

- The World Medical Association Declaration of Helsinki (1996)
- GHP Standard Operating Procedures
- International Conference of Harmonisation Good Clinical Practice (ICH GCP)

The protocol content is structured in line with the Health Research Authority protocol template.

If any issues are disclosed during the interviews that could cause any physical harm for the patient or her child, they will be discussed with the on-call doctor team and, if possible, the patient’s own consultant who would advise on how to manage these matters.

# Research Ethics Committee (REC) and Other Regulatory Review and Reports

Ethical approval will be sought from each of the recruiting sites in Nagpur and then the University of Liverpool. The MOLI RCT will already have been considered by the same ethics committees. The two studies are being submitted separately in order to start the RCT recruitment as soon as possible and because this study focuses on evaluation of both RCT protocols, as well as an overview of women being induced for hypertension in pregnancy in Nagpur’s wider perspectives on induction of labour.

# Regulatory Review and Compliance

Before any site can enrol patients into the study the University of Liverpool and the Chief Investigator will ensure that appropriate approvals from participating organisations are in place.

# Amendments

For any amendment to the study protocol the MOLI team will follow the MOLI protocol amendments SOP.

# Peer Review

The trial protocol will be reviewed by the MOLI Trial Steering Committee (TSC) which comprises of three independent experts and one patient representative, as well as an Indian expert in qualitative research. The MOLI proposal was peer reviewed at the grant application stage.

# Protocol Compliance

Protocol compliance will be managed via the MOLI TSC and TMG via the suite of relevant MOLI SOPS.

# Data Management, Protection and Patient Confidentiality

Data protection and patient confidentiality will be managed via the TSC and TMG via the suite of relevant MOLI SOPS.

Recordings will be made on two password protected digital recorders to guard against equipment failure. These will be anonymised, and attempts will be made to avoid using any identifiable data during the interview. Each participant will be given a code. These recordings will be stored securely within GMC’s research office. Completed audio-recordings will be transcribed and sent in password encrypted files. The recordings and transcriptions will be correctly stored on password protected files on the University computer in accordance with the UK General Data Protection Regulations (GDPR) 2018. Data in other forms e.g. N-VIVO, tree diagrams and excel spreadsheets will all be anonymised and stored in encrypted files, on password protected computers. The data in Nagpur, will be secured on a password protected computer, in a locked room and then also uploaded onto the M drive at the University of Liverpool, so as to ensure a second copy of the data is saved securely. The minimum number of individuals necessary will have access to this data, for quality control, audit and analysis. Any data transferred to co-investigators or sponsors will be anonymised. The data will be stored for 10 years as requested in the University of Liverpool SOPs on record retention. The data custodian will be the sponsor, the University of Liverpool.

All investigators and study site staff must comply with the requirements of the U.K GDPR 2018.

# Patient and Public Involvement

During the study development of the MOLI RCT, a scoping exercise was carried out to assess the potential for the MOLI trial. 14 doctors and 23 women who had undergone induction of labour were interviewed at Government Medical College. Most of the doctors (12/14) and women (22/23) would welcome a change to a misoprostol/misoprostol regimen, but only if it did not increase the risk of CS.

[name], a local consumer representative, who sits on the MOLI Project Steering Committee will review this protocol and interview guides and provide information from a patient perspective*.* She will provide feedback which will be incorporated at the planning stage of this project.

The interview guides have been discussed at length with research assistants (as they spent the most time with patients during the previous INFORM study) and clinicians that have previously worked in Nagpur.

# Access to the Final Study Dataset

The Chief Investigator, Principal Investigator (s), qualitative lead and other qualitative researchers will have access to the full dataset.

# Discontinuation of Study

This study will end on completion of analysis of the data from the last interview of the study (whether patient interview or staff focus group).

In the event that the study is discontinued by the MOLI RCT TSC, participating sites will be advised on any actions that are required with regards to individual participants follow-up. Participants will otherwise be treated according to the usual standard clinical care.

# Withdrawal of Consent

The participant/legal representative is free to withdraw consent at any time without providing a reason and without any detriment to care. The rights and welfare of the participant will be protected by emphasising to them throughout the trial that the quality of medical care will not be adversely affected if they decline to participate or discontinue participation in the trial.

Generally, follow-up will continue unless the participant/legal representative explicitly withdraws consent for follow-up.

Where the participant wishes to withdraw consent, there will be clarification whether this is withdrawal of consent for data already collected or for future data collection. Centres should explain the importance of remaining in trial follow-up and of the importance of contributing data.

# Dissemination Policy

This study will be written up as a separate qualitative paper and as part of the RCT and submitted to peer reviewed journals as soon as possible. The previous INFORM study, undertaken by the same group, was published in the Lancet and other high impact journals. The work will also be presented at national and international conferences. The funders, sponsors and ethical review boards will be acknowledged in the papers. Individual clinicians must undertake not to submit any part of their individual data for publication without the prior consent of the TMG.

Both GHP and the University of Liverpool have active collaborations with the World Health Organization. These relationships will facilitate the consideration of the results of the trial in the development of clinical guidance and guidelines. The University of Liverpool is a WHO Collaborating Centre for Research and Research Synthesis in Reproductive Health, with [name] as the Director of this Centre. [name], co-investigator is a member of the National Institute Health and Care excellence (NICE) induction of labour guideline committee, and co-ordinating editor of the Cochrane Collaboration Pregnancy and Childbirth Group. [name] sits on the advisory committee of the International Federation of Gynaecology and Obstetrics (FIGO). FIGO has access to all of the national professional societies of obstetrics and gynaecologists. In addition, [name] is a member of the Indian professional society, FOGSI. Professors [name], [name] and [name] are on the FIGO expert group on misoprostol dosages.

# Authorship Eligibility Guidelines

Authorship will be attributed according to the amount of work undertaken on this project, currently it is planned that [name] will be the first author. Co-authors will include other members of the q MOLI team including [name] and the MOLI RCT team. [name] is the Chief Investigator.

# Appendices

## Appendix 1- Required Documentation

Qualitative protocol, including interview guides

Patient information sheets

Patient consent form

RCT protocol

CVs all researchers

Contracts U of L, Gynuity, LSTM, GMC, Daga

Ethics approval – GMC, Daga, U of L

## Appendix 2 – Schedule of Procedures for q MOLI
[figure not shown]

## Appendix 3 – Schedule of Procedures for RCT

| **Procedures** | **Screening and study RCT entry** | **Recruitment to randomised trial** | **24 hours after birth** | **Data taken from case notes after discharged End of trial** |
| --- | --- | --- | --- | --- |
| Assessment of eligibility criteria | x | x |  |  |
| Signed consent form | x |  |  |  |
| Qualitative interview (n=12 pre IOL, n=24 post IOL) | x |  | x |  |
| Randomisation |  | x |  |  |
| Administration of study intervention |  | x |  |  |
| Birth |  | x |  |  |
| Maternal complications |  | x | x | x |
| Fetal / neonatal complications |  | x | x | x |
| Serious maternal complications |  | x | x | x |
| Cost effectiveness |  |  |  | x |
| Efficacy of induction process |  |  | x |  |
| Assessment of adverse events |  |  | x | x |
| Mother Generated Birth Satisfaction Index | x |  | x |  |
| Participant Satisfaction Questionnaire |  |  | x |  |

##

## Appendix 4 – Amendment History

| **Amendment No.** | **Protocol version no.** | **Date issued** | **Author(s) of changes** | **Details of changes made** |
| --- | --- | --- | --- | --- |
| .01 | 1.01 | 18.5.20 | [name] | \| Sentence added to study timeframes.  *A few months after study commencement, MOLI and q MOLI study recruitment was halted due to the COVID pandemic. Although the initial focus groups had taken place, the follow-up data collection (planned for 4-6 months after the start of recruitment) had not yet taken place. As a result of ongoing uncertainty, the study period was extended to December 2021.* \| \| --- \| |

## Appendix 5 – MOLI Interview Guide 1: Women, pre IOL

The interviewer will ensure that the participant has consented and is willing to continue. The patient and researchers will move to a private room on the ward. The interviewer will thank the participant for agreeing to be interviewed and will attempt to make them feel as relaxed as possible.

To achieve the study objectives following the semi-structured schedule will be followed. The discussion will be participant-led with prompting questions from the interviewers.

Potential prompts are written in brackets, in italics, which can be used if the patient is not forthcoming with their responses. These do not have to be used, but could help the participant share more information if they are shy.

**Setting of ground rules**

Explain:

- The study and why it is being done
- Tape recording and transcription
- Study numbers/confidentiality
- Use of interpreter, if necessary
- That the participant can stop at any time
- That the participant can refuse to answer questions
- Explain opportunity to ask questions at any time
- Encourage participant be talkative and share their views as much as possible

Check consent form is signed, and the patient is happy to proceed

Check both tapes and start recording

**Interview guide**

Open by stating that we are trying to find out about how women feel about induction of labour, any previous experiences of it and what they know about it. So, we understand that your doctor has recommended induction of labour for you and you are already recruited to the MOLI trial.

- Can you tell me what induction of labour is and what you understand about it? *(Having medications to start labour, what does it mean? Have you heard of it before? What did your doctor say about it to you?)*
- Please can you describe to me the process of labour induction?

*(What will they do to help start your labour? Will they give you drugs? Which ones? Any other methods?)*

- Can you explain why are you having an induction of labour?

*(Having medications to start labour, do you have a medical condition? What is it? What did the doctor say?)*

- How do you feel about it?

*(In your own words tell me what you think about being induced/having medicine to start labour)*

- Can you explain what things are important to you about this process?

*Different things are important to different people and we would like to know what you think, it could be anything from timings, to safety, to place of birth, to the care you receive, to your family’s thoughts, just what you think)*

- Of these things (mentioned in last question), what is the most important thing?

*(The one thing that is the most important thing to you, it could be anything. If you had to choose one aspect, which would it be)*

- Is there anything that you feel particularly positive/happy about this process?

*(Things you were glad about or liked)*

- Is there anything that makes you feel particularly concerned/worried about this process?

*(Things that you didn’t like or made you sad/unhappy/sad about or things that could be better)*

- What do your family members/husband/think about this process?

*(Is anyone in the hospital with you now? What do they think/feel about you being induced?)*

- Have you ever been induced before/any of your relative/friends been induced before?

*(Had the drugs to start labour off, your friends? mother? sisters?)*

- What was your experience/their experiences like? Can you describe them?

*(How did they find it? We’re they happy or sad about it? What do you remember them telling you about it)*

- What do you think being induced will be like for you?

*What do you expect will happen? How do you think you will feel?*

- Can you tell me what you know about how your baby will be monitored (looked after) during labour?

*Will they listen to the babies heart beat during labour? How will they do this? Why do they do this? Is it important?*

- Can you tell me about the different types of fetal heart monitoring?

*(e.g. intermittent auscultation with Pinnard/Doppler or CTG intermittent/continuous)*

- What is important to you about monitoring the baby’s heart beat during labour?

*(How often, how long, straps around your tummy, who does it, why they are doing it, if its normal etc)*

- Do you have any preferences about how your baby is monitored? Why?

*Do any of these methods seem better than others? Or worse? Why? Do any methods appeal to you? Do any methods concern you? Why?*

- In some places around the world staff and women worry that listening to the babies heart beat all of the time in labour, using electronic monitoring, could mean extra false alarms and this means increases in interventions such as caesarean sections, unnecessary tests, or forceps deliveries, which are not needed. How do you feel about this?

*Does that worry you? Is it important to you?*

- If you could choose, how would you like to give birth? *(CS, forceps, normal)* And why?
- As part of the study paperwork you completed the Mother Generated Birth Satisfaction Index, (show the CRF) how did you feel about this process?

*Was it clear? Was it confusing? Was it too long? Or too short? Was it hard to think of the answers?*

- Do you feel that what was written on the form reflects your current thoughts about birth?

*Do the answers on the form reflect your honest thoughts and priorities?*

- Is there anything you want to add or tell me about that hasn’t been discussed?

After completion of the interview/discussion, ask the participant if they have any questions, thank them for their time and stop the recording.

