The ‘Misoprostol or Oxytocin for Induction’ (MOLI) trial is a pragmatic, open-label, randomised trial to compare a misoprostol/misoprostol labour induction protocol with the standard misoprostol/oxytocin protocol. We will recruit approximately 1000 women with hypertensive disease of pregnancy over 24 months in Indian government hospitals in Nagpur, India, in order to randomise 520 to the two RCT treatment arms. All participants will receive oral misoprostol 25mcg 2 hourly for cervical preparation (the first stage of induction). If there is a requirement for a further induction agent after the membranes have ruptured, then the patient will be randomized to receive further oral misoprostol (25mcg 2 hourly) or titrated intravenous oxytocin (standard treatment). The primary outcome for the RCT will be caesarean birth. Secondary outcomes will assess the efficacy of the induction process, maternal and fetal/neonatal complications and the relative cost-effectiveness. Fetal monitoring will be conducted using intermittent auscultation, with electronic fetal monitoring (EFM) in case of abnormalities. EFM has not previously been widely available at the study sites and this is being introduced in 2019. This study therefore provides an opportunity to also assess the staff and patients attitudes to intrapartum fetal monitoring techniques. The primary outcome for the RCT will be caesarean birth. Secondary outcomes will assess the efficacy of the induction process, maternal and fetal/neonatal complications and the relative cost-effectiveness.

This qualitative study will be run alongside the main MOLI RCT in order to explore women’s and health care professional’s experiences and perceptions regarding induction of labour and the two methods compared as part of the RCT. This will be done through semi-structured interviews and focus group discussions.

Qualitative research alongside the quantitative study will provide an in-depth assessment of the study phenomenon [7] both from patients’ and staff perspectives. This will improve external validity, interpretation of results, hearing the individual patients’ voices and potentially cost savings [8].

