**Interview guide**

This aim of this focus group is to gather information from the staff involved in screening, recruiting, randomising and consenting for the MOLI trial in order to gather as much information as possible surrounding the trial and the different regimes. We would like to hear your honest views, so that we can understand the results of the trial better.

Research generally (ice breaker)

Tell me about your experiences of taking part in the trial MOLI Trial so far

Do you feel it will be acceptable to patients?

Do you have concerns/worries about the trial/these protocols?

Can you forsee any potential barriers to recruitment?

Can anyone suggest any potential solutions for any problems?

Can you highlight any areas for improvement?

Tell me about your previous experiences of induction of labour

Any positive?

Any negatives?

How do patients find induction of labour?

What is the hardest part of induction for women?

In this trial there are two treatments, one is a misoprostol/oxytocin regime

Do you have any experience of using this regime?

What were your previous experiences of using the miso/oxytocin regime?

Any positive?

Any negatives?

How do patients find it?

The other treatment in this trial is misoprostol/misoprostol regime, using misoprostol from the start of induction to birth

Do you have any previous experiences of using the miso/miso regime?

Do you have concerns/worries about using it?

How do you think it will work logistically?

As part of the MOLI trial, we plan to have more CTG machines available on labour ward and to do some training about fetal monitoring in labour

What do you currently use for fetal monitoring in your hospital?

How well does this work?

Are there any good things about it?

Any bad things about it?

How do you feel about having CTGs on labour ward?

Do you feel it will change patient care?

How?

Are there any good things about it?

Any bad things about it?

Internationally there is concern that introducing CTG could increase the intervention rate e.g. increase the caesarean rate. How do you feel about this?

Is there anything you want to add or tell me about that hasn’t been discussed?

After completion of the focus group, ask the participants if they have any questions, thank them for their time and switch off the recording.

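### The pre-induction interview guide puts a one-sided statement about electronic monitoring directly before the mode-of-birth question, so that answer may be primed

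*Protocol*

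**What the plan says.** Appendix 5 (Interview Guide 1, women before induction) lists twelve questions about induction and then four open questions about fetal monitoring, ending with "Do you have any preferences about how your baby is monitored? Why". The next main question begins "In some places around the world staff and women worry that listening to the babies heart beat all of the time in labour" and goes on to say, of the electronic method, that it "could mean extra false alarms and this means increases in interventions such as caesarean sections, unnecessary tests, or forceps deliveries, which are not needed". The woman is asked how she feels about this, with the prompt "Does that worry you? Is it important to you". The question after that is "If you could choose, how would you like to give birth", prompted with caesarean, forceps and normal birth. Two questions on the Mother Generated Birth Satisfaction Index and a closing invitation to add anything follow.

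The introduction to Appendix 5 makes only the bracketed italic prompts optional, so the statement is part of the core guide. The same introduction says: "The discussion will be participant-led with prompting questions from the interviewers".

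Appendix 6 (the postnatal guide) contains no comparable statement. It does ask which monitoring the woman would ideally want and which way of delivering a baby she thinks best.

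Specific Objectives lists priorities and expectations about induction (Objective 1) and views on fetal monitoring (Objective 4). Theoretical Framework and Methodology says that themes will be derived inductively.

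**The concern.** The statement gives only drawbacks of electronic monitoring. Its wording is loaded: the resulting interventions are described as unneeded, and the prompt offers worry as the response. Two of the three options prompted in the next question, caesarean and forceps, have just been named as such interventions. A woman who then says she would prefer a normal birth may be giving her own view or echoing the interviewer, and the transcript cannot separate the two.

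This matters more here than in many studies. The Background reports no earlier work on Indian women's views of induction or intrapartum monitoring, and says that electronic monitoring was not previously widely available at the sites. For some women the statement may be among the first things they hear about it. An inductive analysis is meant to find the women's own concerns, and this item supplies one. A second consequence is that women interviewed twice carry the statement into their postnatal interview, while women interviewed only postnatally do not meet it.

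**Working it through.** No power or sample-size figure is involved. The check is the order of the questions and a count of exposed interviews.

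**Order of questions in Appendix 5, as listed**

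1. Twelve questions on induction: understanding, reasons, feelings, what matters and what matters most, positives, worries, family, past experience, expectations. All come before the statement.
2. Four open monitoring questions: what she knows, types, what is important, preferences. All come before the statement.
3. The statement, with its own reaction question. That reaction is exposed.
4. Mode-of-birth preference. It comes directly after and is exposed.
5. Two Index questions: how she found completing it, and whether the form still matches what she thinks about birth. The second is exposed. The woman is told that she has already completed the form, so a shift caused by the statement could look like a failing of the form.
6. Closing invitation.

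So 12 + 4 = 16 main questions precede the statement. None of the four open monitoring questions follows it.

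**Exposed interviews**

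Inputs: 12 interviews before induction and 24 after (Appendix 3 and the Protocol Summary); 6 or more repeat interviews (Post IOL Sampling Frame).

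- Mode-of-birth answers before induction: 12 of 12, if the listed order is followed.
- Postnatal interviews with women who had already heard the statement, minimum: 6/24 = 25%.
- Maximum, if every woman interviewed before induction is interviewed again: 12/24 = 50%.

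These are counts of exposure, not estimates of bias. The totals of 12 and 24 are planning numbers, because Sampling lets saturation decide when interviewing stops; the shares would change with the totals.

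**The case against.** The strongest defence is that the item reports other people's worry and asks for a reaction, which is a legitimate probe. The sentence is attributed and opens conditionally. The interview is participant-led, so the order can vary, and the Protocol allows the schedule to be amended. The preference question just before it has two-sided prompts. Women interviewed twice differ anyway through having had a whole earlier interview, by design, and the group contrast named in the objectives is between the trial arms, not between repeat and single interviewees.

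Most of this is right, and it limits the point. It does not remove it: flexible order does not make the wording neutral, the second half of the sentence is unhedged, and the listed sequence is the one an interviewer will follow by default.

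A reader might infer several stronger things that the Protocol does not support:

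- **That women are told electronic monitoring causes unneeded caesareans.** The text reports a worry and says it could lead to false alarms.
- **That the pre-induction monitoring answers in general, or the answers on induction priorities, are led.** In listed order those questions are already finished.
- **That staff answers on monitoring are led by** "Internationally there is concern that introducing CTG could increase the intervention rate e.g. increase the caesarean rate". In Appendices 7 and 8 this comes after open questions on good and bad aspects, and no open monitoring question follows it. The Amendment History also records that the initial focus groups had already been held.
- **That the randomised trial is affected because** "The primary outcome for the RCT will be caesarean birth". Twelve of about 1000 women is 1.2%. The first interview precedes any ripening drug, and randomisation follows membrane rupture, so exposure cannot depend on the arm.

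**Conclusion.** The point holds in a limited form. The pre-induction guide places a one-sided statement, with a leading prompt, directly before the mode-of-birth question. Three answers are open to priming: the reaction to the statement, the mode-of-birth preference, and the check on whether the Index form matches the woman's current thinking. Between 6 and 12 of 24 planned postnatal interviews would also come from women who had heard it, which bears on their later answers about monitoring and mode of birth.

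This rests on the listed order being followed and on the planned interview numbers. Whether any answer actually shifts is unknown. Mode-of-birth preference is not itself a listed objective, so this is a worthwhile low-cost improvement to the guide and not a threat to the study's main findings on the two regimens.

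**What to change.** - In Appendix 5, ask the birth-preference question before the monitoring questions.
- If the statement is wanted, make it the last substantive item of the pre-induction guide, after the Index questions. Reword it to mention both perceived advantages and worries. For example: some women and staff see advantages in continuous electronic monitoring and some have worries; what do you think? Replace the worry prompt with a neutral one.
- Do not add the statement to Appendix 6. That could expose all 24 postnatal interviews instead of 6 to 12.
- Record which postnatal interviewees had already heard the statement, and take this into account when charting and interpreting their answers on monitoring and mode of birth. Reordering alone does not remove this carry-over.
- Use the same neutral wording in the remaining staff guide (Appendix 8).

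The cost is a minor guide amendment under the study's amendment procedure and re-translation of the changed lines for the women's guide. The staff groups are held in English, so Appendix 8 needs no translation.
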